**Methods:**

This RCT has received approval from The Conjoint Health Research Ethics Board (CHREB) of the University of Calgary (Ethics ID # E-24476). Twenty-four participants treated for a malignancy with autologous stem cell transplant (5 to 18 years) in the Alberta Children’s Hospital will be randomly assigned to an exercise or control group. The exercise group will participate in a two-phase exercise intervention (in- and outpatient) from hospitalization until 10 weeks after discharge. The exercise program includes strength, flexibility and aerobic exercise. During the inpatient phase this program will be performed 5 times/week and will be supervised. The outpatient phase will combine a supervised session with two home-based exercise sessions with the use of the Wii device. The control group will follow the standard protocol without any specific exercise program. A range of outcomes, including quantitative and functional recovery of immune system, cytokine levels in serum, natural killer (NK) cells and their subset recovery and function, and gene expression of activating and inhibitory NK cell receptors, body composition, nutrition, quality of life, fatigue, health-related fitness assessment and physical activity levels will be examined, providing the most comprehensive assessment to date.

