#### Body composition

Standing height and body mass will be measured. We will measure standing height to the nearest 0.1 cm with a clinical stadiometer (SECA, Birmingham, UK), while children stand barefoot. Body mass will be measured to the nearest 0.01 kg using a balance scale (Health o Meter, Illinois, US) with the subjects in their underwear and will calculate body mass index (BMI) as weight height [mass (kg)/height (m^2^)]. Estimated children’s fat-free mass (FFM) will be calculated from the following equation (1): FFM = body mass – fat mass (FM), where FM = 4.95 x Body density (BD) x body mass. Children’s BD will be estimated from skin fold thickness at the triceps, biceps, sub scapular, and suprailiac area. In all subjects, each skin fold will be obtained in duplicate by the same researcher using standard equipment (Harpender skin fold caliper, Bath international, UK) and the mean value per skin fold utilized for statistical analysis [39]. A third skin fold measure will be taken if the difference between the first two measures is greater than 4 mm. Different equations depending on children’s age and gender will be used to calculated BD (1) BD = 1,169 - 0,0788 * log Σ 4 skin folds and BD = 1,2063 - 0,0999 * log Σ 4 skin folds (for boys and girls, respectively, aged ≤12 yr) and (2) BD = 1,1533 - 0,0643 * log Σ 4 skin folds and BD = 1,1369 - 0,0598 * log Σ 4 skin folds (for boys and girls, respectively, aged ≥ 13 yr) [40].

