Systematic reviews support the promising role of EX as a safe and effective intervention to improve HRF and quality of life and fatigue outcomes in children with cancer [3,4]. However, most of the research was performed in children with ALL. Only three articles have been published showing the effect of an EX intervention in children undergoing SCT and the outcomes are promising including improve in cardio respiratory capacity, strength, fatigue and QOL [7,14,15]. This study will provide details about the effect of an EX program on fatigue and QOL as a self-report outcome and also will be compared with parent’s proxy report.

3. The effects of an EX intervention on body composition

The aim of this study is to determine if an early EX intervention during SCT will (a) avoid loss of body weight. Survivors of pediatric patients who went undergoing a SCT are at an increased risk to have less lean mass and an excess of fat mass compared with healthy peers [49].

Given the scarcity of literature on the effect of an EX program on the immune system recovery, QOL, physical activity levels and HRF measures for pediatric cancer patients undergoing SCT, the SCORE study will generate new knowledge and be instrumental in developing future clinical and community-based programming for this population. This will be the largest known study in children undergoing autologous SCT and will provide us with valuable information for a future multisite study. This research could add biologic plausibility to the association between EX and immune system recovery after autologous SCT that may identify new targets for interventions, and inform clinical recommendations for improving survival. Ultimately, this project will enable us to achieve more effective targeted interventions that help pediatric cancer patients achieve healthy levels of PA and HRF and with the hope of optimizing disease and treatment related outcomes.

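### The printed fat-mass equation gives every child a fat mass several times body mass and a negative fat-free mass, and it can reverse the direction of change

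*Protocol article*

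**What the plan says.** The Body composition section (under Health-related fitness assessments) defines FFM as body mass less FM, "where FM = 4.95 x Body density (BD) x body mass". BD comes from the sum of four skinfolds through four equations, by sex and by age (12 or under, 13 or over). For boys aged 12 or under it is "BD = 1,169 - 0,0788 * log Σ 4 skin folds", and for girls of that age "BD = 1,2063 - 0,0999 * log Σ 4 skin folds". The commas are decimal commas. The base of the logarithm is not stated. Reference 40 closes the paragraph, and no other section gives a different rule for FM or FFM.

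The skinfolds are taken in duplicate, with "the mean value per skin fold utilized for statistical analysis". Height and body mass are measured directly and BMI is computed from them.

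The Methods part of the Abstract lists the outcomes: "body composition, nutrition, quality of life, fatigue, health-related fitness assessment and physical activity levels will be examined". The opening of Health-related fitness assessments puts body composition in the fitness battery, and the Secondary purpose names physical fitness.

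**The concern.** Fat mass is part of body mass, so FM must lie between zero and body mass. Body density is close to 1, so a multiplier of 4.95 applied to density times mass puts FM near five times body mass. FFM, obtained by subtraction, is then negative.

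The form of the equation is also suspect. All four BD equations fall as skinfolds rise, yet printed FM rises with BD. Among children of equal weight, the fatter child would be scored as having less fat. Rescaling by a constant would not repair that.

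At stake are the two derived values that split weight into fat and lean tissue. Followed literally, the rule makes both unusable.

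**Working it through.** **Inputs.** From the Body composition section: the FM and FFM rules and the four BD equations. Assumed, because the article gives no values: a sum S of the four skinfolds of 20 to 80 mm (10 to 200 mm as a wider range), and a 30 kg boy aged 12 or under with S = 30 mm as the example. Base-10 logs are used first, then natural logs. The article prints no FM or FFM value, so there is no stated figure to reproduce.

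**1. Example child.**
- BD = 1.169 - 0.0788 x log10(30) = 1.169 - 0.0788 x 1.4771 = 1.0526
- FM = 4.95 x 1.0526 x 30 = 156.3 kg
- FFM = 30 - 156.3 = -126.3 kg

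**2. Printed FM / body mass = 4.95 x BD, lowest to highest over the four equations.**

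| S (assumed) | base-10 log | natural log |
|---|---|---|
| 20 to 80 mm | 5.03 to 5.33 | 3.80 to 4.76 |
| 10 to 200 mm | 4.83 to 5.48 | 3.35 to 4.98 |

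FFM / body mass is 1 minus these values, so it is negative throughout.

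**3. Could any child escape?** FM at or below body mass needs BD of at most 1/4.95 = 0.202. Solving each equation for log S:

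| Equation | log S needed |
|---|---|
| Girls, 12 or under | (1.2063 - 0.202)/0.0999 = 10.05 |
| Boys, 12 or under | (1.169 - 0.202)/0.0788 = 12.27 |
| Boys, 13 or over | (1.1533 - 0.202)/0.0643 = 14.79 |
| Girls, 13 or over | (1.1369 - 0.202)/0.0598 = 15.63 |

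The easiest case is 10.05. That is a skinfold sum of about 10^10 mm in base 10, or about 23 metres with natural logs. The negative FFM therefore depends on neither the assumed skinfold range nor the log base.

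**4. Direction, one input changed at a time (base 10, example child).**
- S from 30 to 40 mm at 30 kg: BD falls to 1.0428 and FM to 154.85 kg, a change of -1.46 kg. The same step at 30 kg in the other equations gives -1.85 (girls, 12 or under), -1.19 (boys, 13 or over) and -1.11 kg (girls, 13 or over).
- Weight from 30 to 28 kg at 30 mm: FM = 4.95 x 1.0526 x 28 = 145.9 kg, so FFM = -117.9 kg, a change of +8.4 kg. FM itself falls, which is the expected direction; only FFM reverses.

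**5. Direction, both inputs changed.** From 30 kg and 30 mm to 31 kg and 40 mm, printed FM changes by +3.70 kg and FFM by -2.70 kg. The likely intended form (step 6) gives +1.58 and -0.58 kg, the same signs.

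**6. Likely intended form (an assumption, not in the article).** A two-compartment model with densities 0.90 for fat and 1.10 for fat-free tissue gives FM = (4.95/BD - 4.5) x body mass. Its constant, 0.90 x 1.10/0.20 = 4.95, is the printed one.
- The example child has FM 6.1 kg (20.3%) and FFM 23.9 kg.
- The two changes in step 4 become +1.33 kg FM and -1.6 kg FFM.
- Over 20 to 80 mm, fat is 9.9% to 37.1% of body mass with base-10 logs. With natural logs the same form gives 65% to 194%, so the log base has to be stated.

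**The case against.** The strongest reply is that this is a transcription slip and not a chosen method. The constant 4.95 points to one familiar form, a source is cited in the same paragraph, and a negative FFM in every child could not pass unseen. The raw inputs are recorded, so both values can be recomputed. Analysts are to be blinded to group. Most of this stands, and it is why the point is minor. It does not remove the point: the sentence is complete, has explicit multiplication signs, and is the only rule given. A symbol lost in text extraction cannot be fully excluded, but one lost symbol would not be enough. A division would have to become a multiplication and a subtracted constant would have to vanish, while the BD equations beside it kept their minus signs.

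Three stronger readings are tempting and are not supported.

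- A reader might infer that the equation always reverses the direction of change. Step 5 shows otherwise: the reversal is certain only when the other input is held fixed.
- A reader might infer a hidden bias in the group comparison, or a replacement formula picked to suit the data. Nothing in the article suggests either.
- A reader might infer from theme 3 of the Discussion, which aims to "determine if an early EX intervention during SCT will (a) avoid loss of body weight", that body composition will be judged on weight alone. The next sentence describes survivors as "at an increased risk to have less lean mass and an excess of fat mass compared with healthy peers", and the lone (a) reads as an unfinished list. No section plans a weight-only assessment, so that wording needs no change on this account.

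Nor is body composition outside the trial's stated purposes. Its place in the fitness battery ties it to the secondary purpose.

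**Conclusion.** The equation is wrong as printed. Negative FFM for every child follows from the article's own equations. The size, FM of about 5 times body mass in base 10 or 3.8 to 4.8 times with natural logs, rests on assumed skinfold sums of 20 to 80 mm. The rule can reverse direction for FM at fixed body mass and for FFM at fixed skinfolds, but not in every combination of changes.

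The reach is limited to derived FM and FFM within the secondary purpose on physical fitness. Natural killer cell activity, the sample size built on it, and measured weight, BMI and skinfolds are unaffected. Confidence is high that the line is wrong and lower on the exact replacement, which must be checked against the source.

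**What to change.** Before analysis:

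1. Check the FM equation against its cited source and correct it. The probable form is FM = (4.95/BD - 4.5) x body mass, to be verified.
2. State the log base in the BD equations.
3. Add a data check that FM lies between 0 and body mass for every child, and that FM rises with the skinfold sum at fixed body mass.

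The cost is one corrected equation, one clarifying word and one range check. No measurement, visit or sample-size change is needed, because body mass and skinfolds are already collected.

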## Discussion

The primary focus of the SCORE study will be to identify the effect of an early EX intervention in the immune system recovery of pediatric patients undergoing autologous SCT. Other important health outcomes will include the intervention impact on QOL and fatigue. We will also be able to examine the mediators and moderators of any observed associations between PA, HRF, and health outcomes after SCT at a mid-term assessment point. Finally, we will be able to identify if an early intervention will be able to diminish the acquisition of a sedentary lifestyle,

Taken together, these data will provide a detailed and complete understanding of the effect of an EX program in pediatric cancer patients undergoing autologous SCT. From our knowledge, this study will be one of the most comprehensive studies in this population, and will provide an initial database along with the impetus to promote a multisite study. A multisite study is the ideal approach to examine the impact of EX on immunological and patient-reported outcomes in the pediatric oncology population, due to relatively small sample sizes at any one centre.

The SCORE study is designed to address the following research themes through pilot data:

1. Hematological and immunological reconstitution and exercise. The primary aim of this project is to examine the associations between EX, recovery of hematological and immunological reconstitution, and the relation with some disease outcomes in pediatric cancer patients undergoing autologous SCT (including duration of neutropenia, thrombocytopenia, anemia, fever, toxicity degree, chemotherapy completion rate infectious complications and event free survival) [41]. The clinical utility of autologous SCT is limited in part by treatment related toxicity [42]. Also, an absolute lymphocyte recovery of 500 cells/μl or more at day 15 after autologous SCT has been reported as a powerful and independent prognostic indicator of clinical outcomes. NK cells have antitumor activity, therefore an early NK cell engraftment with an early anti-tumor immune-surveillance might have a direct impact on survival post autologous SCT. Preliminary studies in children with cancer showed a decrease in NK lytic activity before and after cessation of cancer chemotherapy, especially in those with progressive disease [43,44]. Physical activity has the ability to promote an immune modulation that may involve multiple biological pathways, including a reduction in inflammation, an enhancement of anti-tumor response and may modulate killer cell immunoglobulin-like receptors (KIRs) [45]. Neither of the aforementioned mechanism has been studied in detail [46]. More research is needed to determine which inflammatory mediators and antitumor immune mechanism are more sensitive to EX.

2. Exercise, health-related fitness, quality of life and fatigue questionnaires. The specific objectives of this study are to examine the effect of an EX program on (a) QOL and fatigue outcomes across the SCT process and immediately after discharge, (b) to examine the associations between HRF indices, physical activity and QOL and fatigue outcomes.

Pediatric cancer patients undergoing SCT have an elevated risk for poor QOL and fatigue both during treatment and into survivorship, however this issue has to be studied in depth [4]. Some evidence suggests that EX may be a beneficial tool to improve fatigue and QOL in children with cancer [47]. New research suggest that fatigue is strongly associated with a diminish in physical activity levels [48], thus it is imperative to break the vicious cycle of fatigue in this population.

Systematic reviews support the promising role of EX as a safe and effective intervention to improve HRF and quality of life and fatigue outcomes in children with cancer [3,4]. However, most of the research was performed in children with ALL. Only three articles have been published showing the effect of an EX intervention in children undergoing SCT and the outcomes are promising including improve in cardio respiratory capacity, strength, fatigue and QOL [7,14,15]. This study will provide details about the effect of an EX program on fatigue and QOL as a self-report outcome and also will be compared with parent’s proxy report.

3. The effects of an EX intervention on body composition

The aim of this study is to determine if an early EX intervention during SCT will (a) avoid loss of body weight. Survivors of pediatric patients who went undergoing a SCT are at an increased risk to have less lean mass and an excess of fat mass compared with healthy peers [49].

Given the scarcity of literature on the effect of an EX program on the immune system recovery, QOL, physical activity levels and HRF measures for pediatric cancer patients undergoing SCT, the SCORE study will generate new knowledge and be instrumental in developing future clinical and community-based programming for this population. This will be the largest known study in children undergoing autologous SCT and will provide us with valuable information for a future multisite study. This research could add biologic plausibility to the association between EX and immune system recovery after autologous SCT that may identify new targets for interventions, and inform clinical recommendations for improving survival. Ultimately, this project will enable us to achieve more effective targeted interventions that help pediatric cancer patients achieve healthy levels of PA and HRF and with the hope of optimizing disease and treatment related outcomes.

## Abbreviations

SCORE, (Stem Cell patients Ongoing Recovery through Exercise); SCT, Hematopoietic stem cell transplantation; QOL, Quality of life; EX, Exercise; RCT, Randomized controlled trial; NK, Natural Killer; KIR, Killer immunoglobulin like receptor; HRF, Health-related fitness; PBMNC, Peripheral blood mononuclear cell; DNA, Deoxyribonucleic acid; MFI, Mean fluorescence intensity; PedsQL, Pediatric quality of life inventory; BASC-2, Behavior assessment system for children; AM, Activity monitor; BP, Blood pressure; HR, Heart rate; VE, Ventilation; VCO2, Ventilatory equivalent of carbon dioxide; VT, Ventilatory threshold; RER, Respiratory exchange ratio; RQ, Respiratory quotient; PetO2, End tidal pressure of oxygen.
